### Musculoskeletal baseline assessment

The initial clinical assessment is a musculoskeletal and sports medicine examination. As part of this assessment, a blood sample will be taken (< 20 ml) to analyze relevant parameters of bone and muscle status: The biochemical analysis includes hematologic parameters (hemoglobin, erythrocytes, hematocrit, mean corpuscular volume (MCV), mean corpuscular hemoglobin (MCH), mean corpuscular hemoglobin concentration (MCHC), red cell distribution width (RDW), leukocytes, thrombocytes), serum electrolytes (potassium, sodium, chlorine, calcium, phosphate, magnesium), markers of renal function (creatinine, glomerular filtration rate (GFR)), markers of liver function (γ-glutamyl transferase (GGT)), alkaline phosphatase (ALP), creatine kinase (CK), C-reactive protein (CRP), serum electrophoresis (including albumin, α1-, α2-, β-, and ɣ-globulin) (44). Moreover, urinary creatinine excretion is tested. To evaluate additional metabolic or endocrine diseases, thyroid-stimulating hormone (TSH), gastrin, ferritin, vitamin B12, folic acid, parathyroid hormone (PTH), 25-hydroxycholecalciferol (25-OH-D), osteocalcin, procollagen type 1 n-terminal propeptide (P1NP), bone-specific alkaline phosphatase (BAP), serum bone resorption marker carboxy-terminal collagen crosslinks (CTX), as well as the urinary bone resorption marker deoxypyridinoline/crea (DPD) are measured. In addition, pyridoxal-5-phosphate (PLP) levels are evaluated as a potential indicator of a reduced ALP activity [44]. Depending on the clinical examination and skeletal risk profile of the athletes, the physicians will decide on further examinations to assess bone quality (e.g., bone densitometry and/or bone microstructure analysis) [45].

### Continuous data collection during the season

During the season each participant will be equipped with one IMU (SmarTracks Diagnostics DX 5.0, Humotion GmbH, Muenster, Germany) and a belt for application on L5. The IMU should be worn in every training session and during competitions/races. To verify the sensor's data, a training diary will be collected after each run to record the subjective load measured by the Perceptual Wellness Questionnaire [46], and Rating of Perceived Exertion [47] as well as information about training content and conditions (environment, shoes, surface, etc.). Objective load data including distance, time, and velocity will be collected by the athletes’ running watches and the following upload on a social network app (www.strava.com). Injury monitoring is performed by the Oslo Sports Trauma Research Center Questionnaire in its German version [48–50] and will be answered by the athletes once a week. The questionnaire and the training diary will be provided via the app AthleteMonitoring (athletemonitoring.com; FITSTATS Technologies, Inc., Moncton, N-B, Canada).

In case of an injury, athletes will be advised to visit the participating sports medicine physicians for adequate medical diagnosis, possible imaging, and therapy. Furthermore, the above-mentioned biomechanical laboratory assessment will be repeated if possible (determined by mutual decision of participant and sports medicine physicians). To control recovery after the occurrence of an injury the athletes have to answer the University of Wisconsin Running Injury and Recovery Index in its German version [51, 52].

### Outcomes

The primary outcome of the study is the occurrence of injuries to analyze their association to biomechanical, skeletal, or loading parameters by machine learning.

In more detail, the outcome of the study will be presented as:Incidence and severity per 1000 exposure hours of overall injuries in competition and training of running athletes.Prevalence of nutritive deficits (e.g., vitamin D deficiency) and skeletal alterations. Relationship between clinical baseline assessment and incidence of bone stress injuries during the study period.Identification of individual running patterns (stride length, cadence, ground contact time, tibial shock, and tibial acceleration) measured by IMUs and analysis of the relationship between biomechanical running parameters and the incidence of running-related injuries.Analysis of further influencing variables (training periodization, subjective stress perception, objective stress, gender, running experience, surface, etc.) on the incidence of running-related injuries.Biomechanical changes occurring before and after an injury

### Data processing

All collected data will be anonymized, stored, and saved in the main computer, password-protected. A weekly log will be controlling for new injuries throughout the season. As mentioned, the questionnaires will be available from digital means to the researchers, as well as the clinical personal data.

The synchronized data from the laboratory-based assessments will be processed in Visual3D (C-Motion Inc., Germantown, MD, USA), according to the overground running trials, and the instrumented treadmill run. A Visual3D report will be created based on commonly reported foot strike and toe-off events, including but not limited to kinematic and kinetic data (Table 1). Similarly, IMU data will be processed in Matlab or Pyhthon 3 and a biomechanical report will be created as well.

The reference data from the Humotion IMU will be stored in the SmarTracks Diagnostics DX 5.0 software (Humotion GmbH, Muenster, Germany) on the main computer. Post-processing will be carried out from the 9 channels (accelerometer, magnetometer, and gyroscope) by in-house algorithms from Humotion GmbH.

A master data table will be created with all available variables, categorized by subject and per day/week (continuous IMU season data and daily/weekly questionnaires), including a column to indicate if the subject suffered an injury (injury label).

### Statistical analysis

Data cleaning, feature selection, and validation will be processed, then multivariate analyses and machine learning methods might detect data changes related to an injury. Moreover, demographic and anthropometric data will be processed with descriptive statistics. Characteristics of the population regarding gender or other group variables will be compared using t-tests, Wilcoxon signed-rank tests, X^2^ tests, or Fishers' exact test according to their parametric or non-parametric distribution (injured vs non-injured groups). The statistical analysis will be performed using statistical software R (http://www.R-project.org) or SPSS 25 (SPSS Inc., Chicago, Illinois, USA). The level of significance will be set at *p* < 0.05.

Also, other dimensionality reduction techniques might be employed, such as Principal Component Analysis, to set the weight of certain variables into the machine learning models.

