## Background

Running is one of the most popular sports worldwide. Despite strong evidence for the health benefits, the incidence of musculoskeletal overuse injuries remains high. In a recently published systematic review, almost half of the 22,823 runners sustained an injury during the respective observation period [1]. Depending on the study design and investigated cohort the injury rates vary between 19–79% [2, 3]. For instance, long-distance runners but also novice runners are more susceptible to sustain an injury compared to short-distance runners, and recreational runners [4, 5]. No difference, however, was found for the overall injury rate in females (20.8 injuries per 100 runners) and male runners (20.4 injuries per 100 runners) [6].

Many studies have methodological weaknesses, e.g., retrospective data collection, lack of load monitoring, lack of multivariable analysis of external and internal risk factors, or diagnosis based on patient self-report [3, 7]. Furthermore, the multifactorial influence of external and internal risk factors on musculoskeletal injuries—e.g., bone stress injuries, tendinopathies, and muscle injuries—has not yet been sufficiently clarified [8, 9]. Despite the multifactorial nature, the underlying etiology of overuse injuries can be explained by an imbalance between load and recovery [7, 10, 11]. Thus, runners with rapidly increased training volume as well as runners with too low training intensity showed an increased risk of injuries [12, 13]. Based on this information, the identification of risk factors for the development of running-related injury should occur simultaneously with objective training load monitoring.

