## Methods

### Study design

The athlete’s injury monitoring and determination of the internal and external risk variables will be conducted in a prospective observational cohort study. During a season (approximately ten months), 120 athletes will be monitored for injuries, internal and external load, and biomechanical running parameters (Fig. 1). The study will be performed following the Good Clinical Practice guidelines [29] and in line with the Declaration of Helsinki. The present study protocol is prepared according to the Standard Protocol Items: Recommendations for Interventional Trials (SPIRIT) 2013 Statement [30].

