## Discussion

The study described in this protocol will aim to use prospective injury data collection over a complete season period to (a) assess running injuries and their characteristics, (b) identify and analyze internal and external risk factors as well as identify their interaction, and (c) determine and predict the relationships between internal and external risk factors and running-related injuries using machine learning processes in running athletes.

Considering different running distances and levels, a recent systematic review from 18 prospective studies showed an overall incidence of 40.2% ± 18.8% for running-related musculoskeletal injuries [1]. In over 70% of the running-related injuries, overuse injuries are located at the knee, ankle, lower leg, foot, and toe [1, 55]. For instance, the occurrence of a skeletal overuse injury is related to loading patterns that lead to microdamage and tissue fatigue, and finally to a bone stress injury [56, 57]. The mechanical overloading can develop during multiple sessions (gradual onset) or in a single session (sudden onset) and is dependent upon the structure-specific load capacity [15]. As a result of an imbalance of the mechanical load and the structure-specific load capacity, pathologies such as patellofemoral pain syndrome, plantar fasciopathy, iliotibial band syndrome, bone stress injury, or Achilles tendinopathy can occur [1, 55]. To prevent such pathologies a detailed analysis of the risk factors is necessary. Among others, significant risk factors in running are: previous injuries, higher body mass index, low vitamin D status, impaired bone health [16, 17], higher age, sex, no previous running experience, lower running volume and biomechanical factors [8, 9, 43]. All of these risk factors are in some way attributable to a mismatch of loading and loading capacity.

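### The only rank test named for comparing injured with non-injured runners is the Wilcoxon signed-rank test, which needs matched pairs that the protocol does not create

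*Protocol article*

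**What the plan says.** The relevant sentence is in the protocol article, Methods, Statistical analysis. Its subject is "Characteristics of the population regarding gender or other group variables". These "will be compared using t-tests, Wilcoxon signed-rank tests", chi-square tests or Fisher's exact test, with the choice made "according to their parametric or non-parametric distribution (injured vs non-injured groups"). The section then sets the threshold: "The level of significance will be set at *p* < 0.05".

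Study design describes a single cohort: the work "will be conducted in a prospective observational cohort study", in which "120 athletes will be monitored for injuries, internal and external load, and biomechanical running parameters". Participants describes recruitment through clubs, associations, social media and running stores, with no matching of one runner to another. Data processing adds an injury label as a column of the master data table. No rank-sum or Mann-Whitney test is named anywhere in the article.

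**The concern.** The test and the comparison stand in the same sentence and do not fit each other. The signed-rank test takes one difference per pair, ranks the absolute differences and sums the ranks by sign. It needs either one sample or two measurements that belong together. Injured and non-injured runners, or women and men, are disjoint sets of people, and nothing links a given member of one set to a given member of the other. This would be so even if the two groups happened to be the same size.

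At stake is the conventional group comparison of runner characteristics wherever a continuous variable is judged non-normal. An analyst who follows the text literally either cannot run the test or must invent a pairing. The reported p-value then depends on how the file was sorted, and some runners in the larger group are left out.

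**Working it through.** The plan gives no power or group-size figure for this comparison, so there is none to reproduce. The check asks what happens if the named test is applied to groups of the size the article's own incidence figures imply.

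**Inputs from the article**
- Total: 120 athletes (Study design).
- Injury proportion, point value: a cited review "showed an overall incidence of 40.2% ± 18.8% for running-related musculoskeletal injuries" (Discussion).
- Injury proportion, range: "the injury rates vary between 19–79" per cent (Background).
- Threshold 0.05 (Statistical analysis). Two-sided testing is assumed, because the article does not say.

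**Group sizes** (120 × proportion)
- 40.2%: 120 × 0.402 = 48.2, so about 48 injured and 72 not.
- 19%: 120 × 0.19 = 22.8, so about 23 and 97.
- 79%: 120 × 0.79 = 94.8, so about 95 and 25.
- The groups are equal only if exactly 60 runners are injured.

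**Can the test be computed?** Given 48 and 72 values, a standard routine for the signed-rank test (Python's scipy) stops with an error because the two lists differ in length.

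**Runners lost if pairing is forced**
- 48 v 72: 72 − 48 = 24 dropped, which is 24/120 = 20% of the cohort.
- 23 v 97: 97 − 23 = 74 dropped.
- 95 v 25: 95 − 25 = 70 dropped.

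**Precision for a difference in means** (unit variance, unrelated runners)
- All runners, 48 v 72: 1/48 + 1/72 = 0.0347.
- 48 arbitrary pairs: 2/48 = 0.0417.
- Ratio: 0.0347/0.0417 = 0.83.
- At 23 v 97: (1/23 + 1/97)/(2/23) = 0.0538/0.0870 = 0.62.
- At 95 v 25: (1/95 + 1/25)/(2/25) = 0.0505/0.0800 = 0.63.

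**Simulation** (10,000 data sets per setting, normal data, 48 v 72; the 0.5 SD shift is an illustrative assumption)

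| | Rank-sum, all 120 | Signed-rank, 48 arbitrary pairs |
|---|---|---|
| Type I error, no shift | 0.048 | 0.046 |
| Power, 0.5 SD shift | 0.74 | 0.65 |

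**Dependence on row order.** One simulated data set with a 0.5 SD shift was paired at random 2,000 times. The signed-rank p-value ran from 0.000007 to 0.050, with a median of 0.0013. The rank-sum test gave a single p-value of 0.0003 on the same data.

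The type I error holds for a simple reason. If the two groups have the same distribution and the pairing is unrelated to the values, the difference between two unrelated runners is symmetric about zero, which is what the signed-rank test assumes.

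**The case against.** The strongest defence is that the article does contain paired data: measurements at the start and end of the season (Assessment procedure) and biomechanics before and after an injury (Outcomes). A signed-rank test would suit those. But the sentence does not refer to them. It concerns characteristics by group and names the groups, so this defence fails.

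A second defence is that the phrase is a slip for rank-sum, and that software would expose it as soon as the groups differ in size. That is plausible and lowers the practical risk. It does not make the published rule correct. Nor can the point be left to a separate analysis plan, because the article names a specific test, and a plan naming another would contradict it.

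The objections to a wider reading do stand:
- A reader might infer that every skewed marker, training measure and questionnaire score goes through this test. The sentence covers population characteristics and lists no variables. Outcomes assigns the association of biomechanical, skeletal and loading parameters with injury to machine learning.
- A reader might infer that the resulting p-values are meaningless or inflated. The simulation does not support this: type I error was 0.046.
- A reader might take unequal group sizes as part of the plan. They are only an expectation drawn from cited incidence figures. The defect is the absence of pairs.
- A reader might want the t-test specified as the Welch version. That is a preference. An unqualified t-test beside two named independent groups is not an error.

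**Conclusion.** The rule is wrong as written, with low to moderate severity. The only rank test named for comparing independent groups requires matched pairs, and the design supplies none. The consequence is either a test that cannot be computed or one with an order-dependent p-value, discarded runners and reduced power. Type I error stays near nominal when the pairing is arbitrary.

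The figures of 24 dropped runners, a variance ratio of 0.83, and power of 0.65 against 0.74 are illustrations. They rest on the 40.2% incidence. The ratio applies to means with equal variances, and the power figures to normal data with a 0.5 SD shift. For skewed variables the loss could be larger or smaller, and towards either end of the 19–79% range the groups become more unequal and more runners would be dropped.

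The primary analysis, the machine-learning model of injury occurrence, does not depend on this sentence. Nor is any sample size or risk-factor ranking stated to depend on it.

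**What to change.** In Statistical analysis, replace the Wilcoxon signed-rank test with the Wilcoxon rank-sum (Mann-Whitney U) test for the injured versus non-injured and gender comparisons, and describe the accompanying t-tests as independent-samples. If within-runner comparisons are to be tested (baseline against end of season, or before against after an injury), add a separate sentence that assigns the signed-rank or paired t-test to them. The cost is a change of one phrase and at most one added sentence, with no effect on data collection, sample size or the primary analysis.

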### Machine learning models

The collected data will be analyzed using the probabilistic ML model Deep Gaussian Covariance Network (DGCN). For this purpose, all measured sensor data are used as input parameters $$X$$ after their processing. The output parameters $$Y$$ represent for example the ground contact time as well as other variables derived to determine the injury risk. The model learns the functional relationship $$Y = \hat{f}\left( X \right) + \in ,$$ where $$\in$$ represents the possible model error. Thereby $$\hat{f}\left( X \right)$$ is a Gaussian process ($${\mathcal{G}\mathcal{P}}$$): $$\hat{f}\left( X \right)\sim {\mathcal{G}\mathcal{P}}\left( {\mu \left( X \right), K\left( {X,X} \right)} \right)$$ with its mean function $$\mu \left( X \right)$$ and its covariance matrix $$K\left( {X,X} \right)$$. In the DGCN approach, the free parameters in this model, as well as the covariance matrix, are determined by a coupled neural network such that all free parameters (which must be trained in order to learn the relationship between $$X$$ and $$Y$$) are dependent on the data point to predict (see Fig. 2 for a schematic overview of the coupling). This enables the model to represent non-stationary relationships between $$X$$ and $$Y$$ in a way that most other stationary methods cannot. For example, when the relationship between $$X$$ and $$Y$$ changes due to approaching injuries or different running behaviors such as sprints. In contrast to standard Gaussian processes that can only be applied to a limited number of data points, DGCN can apply the Gaussian process to any number of data points due to its coupling with neural networks. This is possible because batch training can be applied as is common with neural networks. In addition, DGCN allows taking into account the time history of the past data like recurrent neural networks (RNN) can [53].

**Fig. 2 Fig2:**
[figure not shown]
Schematic overview of the DGCN model

After the model has been trained, it can be used for new predictions such as injury risk prediction. The already mentioned advantage of a probabilistic ML model is that the uncertainty of the predicted injury risk can also be given, e.g., in the form of a confidence interval. For example, a high predicted injury risk with a wide confidence interval can be less dangerous for the runner than a medium injury risk with a very narrow confidence range. This type of prediction evaluation is not possible with non-probabilistic modeling approaches.

Finally, methods of global variance-based sensitivity [54] analysis will give us a deeper understanding of the learned relationships between the input signals and, for example, the risk of injury. The influence or importance of the input parameters used in the model on the output variable is determined with the help of the model. As a result, ranking of the important parameters is possible as shown in Fig. 3. Also shown in this figure is the trained DGCN model as a function of the two most important input parameters and the output variable to be mapped. The transparent areas represent the 95% confidence interval of the model. Such plots can also provide a deeper understanding of the interdependencies of the parameters.

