**Methods:**

The prospective longitudinal cohort study will include competitive adult athletes, running at least 20 km per week and being free of injuries three months before the start of the study. At baseline and the end of the study period, subjective questionnaires (demographics, injury history, sports participation, menstruation, medication, psychology), biomechanical measures (e.g., stride length, cadence, kinematics, kinetics, tibial shock, and tibial acceleration) and a medical examination (BMI, laboratory: blood count, creatinine, calcium, phosphate, parathyroid hormone, vitamin D, osteocalcin, bone-specific alkaline phosphatase, DPD cross-links) will be performed. During the study period (one season), continuous data collection will be performed for biomechanical parameters, injuries, internal and external load. Statistical analysis of the data is performed using machine learning (ML) methods. For this purpose, the correlation of the collected data to possible injuries is automatically learned by an ML model and from this, a ranking of the risk factors can be determined with the help of sensitivity analysis methods.

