To address the multifactorial causation at an interindividual level of risk factors, this study will perform an ML analysis including the discriminative mediators. The advantage of using ML processing is that the model is able to learn from the input data which means, usually ML results in a training phase and a test phase [24]. Feeding ML models with human biomechanical data, especially from IMUs, is already a common practice in activity recognition [64–66], however, the goal in the present study is to input both kinematic and descriptive data to the ML model and to generate injuries as output data to predict the injury risk. Van Eetvelde and colleagues (2021) recently published a systematic review about ML methods to predict and prevent injuries in team sports [23]. The most frequent ML methods used in the included studies were tree-based ensemble methods, Support Vector Machines, and Artificial Neural Networks, resulting in an injury prediction from poor (Accuracy = 52%, AUC = 0.52) to strong (AUC = 0.87, f1-score = 85%) [23]. Based on this systematic review, it can be concluded that the use of ML models for the prediction of risk factors seems to be appropriate.

To the best of our knowledge, no study investigated prospectively the influence of biomechanical, skeletal, and loading risk factors on running-related injuries via machine learning algorithms in running athletes. The results of the planned study may deliver a substantial impact on the early detection of risk factors for running-related injuries. Thus, runners could react to increased risk during training routine by wearing the IMU and using the ML system and actively contribute to minimizing the incidence of injuries in running. Future studies should focus on the system-implemented recommendations in case of an identified increased risk of injury.

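### The risk-factor ranking divides up the trained model's own output variance, so its size does not show whether the model predicts injury

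*Protocol article*

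**What the plan says.** The abstract (Methods) says the model learns how the collected data relate to injuries and that, from this, "a ranking of the risk factors can be determined with the help of sensitivity analysis methods". The section on machine learning models names the tool: "methods of global variance-based sensitivity [54] analysis will give us a deeper understanding of the learned relationships". It continues: "The influence or importance of the input parameters used in the model on the output variable is determined with the help of the model". The result is stated next: "As a result, ranking of the important parameters is possible as shown in Fig. 3".

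The only uncertainty described alongside the ranking is that of the fitted surface plotted against the two top inputs: "The transparent areas represent the 95% confidence interval of the model".

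Three other places bear on the point:

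- The model output is introduced with an example that is not injury; the outputs "represent for example the ground contact time as well as other variables derived to determine the injury risk". The Discussion, in contrast, names injuries as the output.
- The Statistical analysis section mentions validation in general terms: "Data cleaning, feature selection, and validation will be processed".
- The Discussion remarks that "usually ML results in a training phase and a test phase".

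Neither the validation nor the test phase is linked to the ranking. The 0.05 significance level stands with the comparison of injured and non-injured groups.

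**The concern.** A variance-based index answers this question: of the variation in the fitted function, how much is due to this input? That is a property of the fitted function and of an input distribution. Observed injuries shape it only through the fitting. At the ranking step the index is divided by the model's own output variance, so a model that has learned noise and a model that has learned a real relationship can give indices of similar size.

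The article calls the product a ranking of risk factors, and its Discussion foresees runners acting on risk identified by the system. If the ranking is reported as described, a list of leading parameters can come out of data in which none of them is related to injury, and nothing attached to the list would reveal this.

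**Working it through.** The article gives no threshold, error rate or worked index for the ranking, so there is no figure to reproduce. The check is to apply the stated rule where no input is related to injury.

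**Inputs**
- Runners: 120 (Study design).
- Proportion injured: 40.2% (Discussion), varied to 19% and 79% (Background).
- Number of inputs p: 5 (the IMU parameters in the running track section) or 23 (entries counted in Table 1).
- Assumptions not in the article: one row per runner; independent standard-normal inputs; injury drawn independently of all of them; a linear model as stand-in for the planned network.

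**Formula.** For a linear fit with independent, unit-variance inputs, the index of input j is

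S_j = b_j² / Σ b_k²,

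where b_j is the fitted coefficient. These sum to 1 whatever the quality of the fit. With no effect, the b_j are approximately independent normal with mean zero and equal variance, so S_j behaves like Z_j² / Σ Z_k² with Z standard normal. Neither the number of runners nor the injury proportion appears in that expression, so recruiting more runners does not shrink the top share.

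**Results with no effect (2,000 runs per setting, 40.2% injured)**

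| Inputs | Median top share (5th–95th percentile) | Top three together | AUC, training data | AUC, new data |
|---|---|---|---|---|
| 5 | 0.53 (0.34–0.83) | 0.95 | 0.61 | 0.50 |
| 23 | 0.21 (0.14–0.34) | 0.48 | 0.76 | 0.50 |

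A separate simulation gave 0.52 and 0.21. At 19% and 79% injured the medians were again about 0.53 and 0.21. The normalised-squares formula gives 0.533 and 0.211.

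**Does a real effect stand out?** In a ridge logistic stand-in with 23 inputs, the median top share was 0.21 with no effect, 0.22 with one true factor of 0.3 SD and 0.26 with one of 0.5 SD. The no-effect range in the table, 0.14–0.34, covers all three.

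**Dependence on the model.** A Gaussian process with one length scale per input gave larger values with no effect: median top total-order index 0.88 (5 inputs) and 0.66 (23 inputs), AUC 0.50 in new data. In a separate set of Gaussian-process runs with 23 inputs the training AUC was 1.00. This stand-in overfits heavily, so its values are not used to size the point. It collapsed to a constant, leaving no index, in 6 of 100 runs with 5 inputs and 0 of 30 with 23.

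**Does a null reference help?** In the linear model, an input was named only if the largest un-normalised index exceeded the 95th percentile of its permutation distribution (199 shuffles of the injury labels, 600 runs). With no effect, at least one input was named in 5.7% (5 inputs) and 6.0% (23 inputs) of runs, Monte Carlo standard error about 0.9 points.

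**The case against.** The strongest reply is that this is an article. It mentions validation and a test phase, and the full protocol or analysis plan may tie them to the ranking. The section itself speaks of deeper understanding and says only that a ranking is possible, which is close to descriptive use. This limits the point to the ranking as stated and rules out any claim that validation is absent. It does not remove the point, because the article chooses a measure and says what it yields, and that measure alone cannot yield it.

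Four stronger readings are tempting and are not supported:

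- *The rule names risk factors in every data set.* It does not when the fit is constant, as in 6 of 100 Gaussian-process runs with 5 inputs. Moreover, any ranking has a first place.
- *Injuries play no part.* They enter through fitting when injury is the output. In a Gaussian-process simulation, one true 0.5-SD factor ranked first in 28% of runs with 23 inputs, against 1/23 = 4% by chance. The order carries some information.
- *The objectives on risk factors rest on this ranking alone.* The Outcomes and Statistical analysis sections plan other injury analyses, including comparisons of injured and non-injured runners, which use observed injuries and can come out null.
- *The shares above are what the study will see.* The plan uses daily or weekly records, time history and a different model.

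The prediction interval in the Fig. 3 type of plot may warn a reader that the surface is uncertain, but it is not an interval on an index or a rank.

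**Conclusion.** The point holds in limited form. As described in the abstract and the machine learning section, the ranking comes from indices normalised by the fitted model's own variance, with no stated link to held-out injury prediction or to a null reference. With no association, a non-constant fit still yields a ranked list. In the linear illustration the leading input takes a median of about 0.53 of the variance with 5 inputs and 0.21 with 23, at AUC 0.50 in new data.

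Those values rest on 120 runners, one row each, independent inputs and a linear stand-in; the Deep Gaussian Covariance Network was not tested. What does not depend on these choices is that the normalised size of an index does not show whether the model predicts injury. The plan should be changed on this, but the change concerns how the ranking is qualified and labelled, not the study's data or its other analyses.

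**What to change.** In the machine learning section:

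1. Call the ranked inputs risk factors only if the injury model's performance in runners not used for fitting exceeds that of the same pipeline refitted after permuting whole injury records between runners (one-sided 5%). Otherwise report that there is no evidence that the ranking reflects injury.
2. Present the variance-based indices and the Fig. 3 type of plot as a description of the fitted model, next to the held-out performance.
3. If individual inputs are named, rank them by the loss of held-out performance when the input or input group is permuted. Give intervals from resampling runners, with a max-statistic or similar control for multiplicity.

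The permutation scheme is one workable option; any reference that uses observed injuries in unseen runners would serve. Step 3 has not been simulated.

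**Cost.** A few sentences and computing time; no new data or participants. With 10 folds and 99 permutations, step 1 needs 10 × (1 + 99) = 1,000 fits, which is not trivial for a deep model on season-long records.

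**Power of step 1** in a ridge stand-in with one row per runner (400 runs), at 23 and 68 inputs (68 = 23 in Table 1 + 40 blood and urine markers + 5 IMU parameters):

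| True factors | 23 inputs | 68 inputs |
|---|---|---|
| None | 4.8% | 5.3% |
| One of 0.5 SD | 20% | 13% |
| Five of 0.5 SD | 94% | 64% |

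A single moderate factor would usually be missed, so a negative result must not be read as absence of risk factors.
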